#### Data analysis

We will seek to adhere to the steps proposed in the modelling phase of the Medical Research Council guidelines for developing complex interventions.^42^ The purpose of a feasibility study is not to make a formal analysis of the primary outcome, but to evaluate trial processes to determine whether to progress to a study of effectiveness and to estimate parameters needed to design the future trial.^42^ Data analysis will be conducted by a researcher who has not been involved with the intervention itself and who is blinded to the arm allocation. Double data entry and checking will be used to ensure accuracy.

We hypothesise that the intervention is feasible and might be able to improve knowledge, attitudes and intended behaviour in relation to dementia among CHWs. Analysis of quantitative data will be based on ‘intention to treat’, that is, data from all participants will be included regardless of their withdrawal from the study or not. Descriptive analysis will include central and dispersion measures, according to the types (eg, continuous, categorical, nominal) and distribution patterns of the variables, including number of incomplete responses and dropouts, ceiling and floor effects. Differences in levels of variables related to dementia stigma, namely, knowledge, attitudes and intended behaviours towards people living with dementia, before and after the intervention, between groups and between time points (t0 and t2), will be analysed using Student’s t test or a non-parametric test, according to data distribution. We will measure internal reliability (Cronbach’s alpha) and test–retest, levels of variance, correlation between sociodemographic variables and between the different outcome variables. An appropriate statistical approach will be chosen to handle any missing data depending on its pattern and type of variables.

Quantitative feasibility measures will be analysed descriptively and will be compared with the results from the outcome measures. Feasibility data collected through qualitative methods will be analysed in an integrated manner using content analysis as well as triangulation techniques in NVivo.^43 44^ In preparation to that, semistructured interviews will first be transcribed anonymously and verbatim.

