**Methods and analysis:**

This will be a randomised controlled feasibility trial conducted with 150 CHWs from 14 primary care units (PCUs) in São Paulo, Brazil. PCUs will be randomly allocated (1:1) in two parallel groups—experimental group or control group. Participants from PCUs allocated to the experimental group will receive a 3-day group intervention involving audio-visual and printed materials as well as elements of social contact. The control group will keep their usual routine. Knowledge, attitude and intended behaviour stigma-based outcomes will be assessed at baseline and at follow-up (30 days after intervention) to both groups, with additional questions on feasibility for the experimental group at follow-up. Around 10–15 participants will take part in follow-up semistructured interviews to further explore feasibility. Quantitative analyses will follow an ‘intention to treat’ approach. Qualitative data will be analysed using content analysis.

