### Participants and sampling

All CHWs in each of the 20 eligible PCUs located in São José dos Campos will be invited to take part. Individuals working as a CHWs for less than 3 months will be excluded. Each PCU has approximately from 8 to 12 CHWs, totalling 160 to 240 potential participants. A proportion (30%) of refusals to participate and dropouts are expected (eg, change in work schedules); therefore, we estimate to include approximately 14 PCUs involving around 150 participants in the trial.

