#### Feasibility assessment

First, a brief evaluation will be conducted on the last day of the intervention through discussion and notes will be taken by the researchers (eg, relevance, positive and negative aspects). Then, in t2, additional measures (objective and subjective) regarding the feasibility of the intervention will be applied, including a measure of satisfaction with the intervention^38^ and open questions (details in online supplemental material II). We will also collate information on recruitment rate and retention overall and per session, intervention completion rate, evaluation measures completion, appropriateness/acceptability and fidelity of the intervention. Provisional decision rules for what procedures to carry through to the full trial will include: retention of at least 70% completing at least two-thirds of the sessions, less than 15% missing on outcome measures and fidelity of at least 75% according to a fidelity checklist to be completed by a member of the research team in every session.^39–41^ Qualitative and quantitative findings will be collated and reported in a transparent, and the decision regarding whether the intervention is feasible or not will be taken (plus justified and reported) on discussion among the research team.

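### The all-participants intention-to-treat promise is not delivered by the named t or rank tests alone; it rests on an unnamed missing-data approach to be chosen from the pattern of missingness

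*Protocol article*

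**What the plan says.** The abstract of the protocol article states that "Quantitative analyses will follow an ‘intention to treat’ approach". The Data analysis section defines the term: "data from all participants will be included regardless of their withdrawal from the study or not". In the same paragraph, differences in knowledge, attitudes and intended behaviour, between groups and between t0 and t2, "will be analysed using Student’s t test or a non-parametric test, according to data distribution". No other analysis of the arm comparison on these outcomes is named. The paragraph ends: "An appropriate statistical approach will be chosen to handle any missing data depending on its pattern and type of variables".

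Two figures elsewhere bear on how many scores might be absent. The provisional decision rules under Feasibility assessment include "less than 15% missing on outcome measures". Participants and sampling says "A proportion (30%) of refusals to participate and dropouts are expected" and uses this to arrive at about 14 units and about 150 CHWs.

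**The concern.** A t test or rank test compares the values it is given. Unless something else is done first, a between-group comparison at t2 uses only people with a t2 score, and a before-after comparison uses only people with both scores. The definition of intention to treat covers everyone, whether or not they withdraw. The named tests do not meet that definition by themselves, so the missing-data step has to do it. That step is left open, and its choice is tied to the missingness that will be seen. Nothing in the wording requires a method that keeps everyone; a complete-case analysis would also satisfy it.

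The stakes are modest but real. Data analysis gives, as one purpose of the study, estimating the parameters needed to design the future trial. Loss could plausibly differ by arm, because the experimental arm is asked for 9 hours over 3 days and the control arm for questionnaires only. A completer comparison reported as intention to treat could then carry a shifted between-group difference into the next trial's design.

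**Working it through.** **Inputs.** Eligible units: 20. Combined refusals and dropouts: 30%. Planned sample: about 14 units and about 150 CHWs. CHWs per unit: 8 to 12. All are from Participants and sampling. Tolerated missing outcome data: just under 15% (Feasibility assessment), read here as the share of CHWs without a usable outcome score.

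**The plan's own figure.** 20 × (1 − 0.30) = 14 units, which reproduces the stated number. For participants, 14 × 8 = 112 and 14 × 12 = 168. The stated 150 lies inside this range and corresponds to 150 / 14 = 10.7 CHWs per unit. The 30% is therefore already spent in reaching the sample.

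**Who enters each named comparison, on observed data.**
- Between groups at t0: needs t0 only, so nobody is lost for lack of t2.
- Between groups at t2: needs t2.
- Change from t0 to t2, within or between groups: needs both.

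**Numbers lost at the protocol's limit.** 150 × 0.15 = 22.5. Staying below 15% therefore means at most 22 CHWs missing, leaving 150 − 22 = 128. The standard error grows by a factor of 1 / √0.85 = 1.08, so the loss of precision is small. The issue is possible bias.

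**Bias in a completer comparison.** In one arm, completer mean − full mean = fraction lost × (mean of completers − mean of those lost). The protocol gives no value for the last term. Suppose, as an assumption, that those lost from the experimental arm would have scored 0.3 to 0.5 SD worse than completers, with no such difference in controls:
- 0.15 × 0.3 = 0.045 SD
- 0.15 × 0.5 = 0.075 SD

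If the same fraction and the same difference applied in both arms, the two terms would cancel. If those lost would have scored better, the sign would reverse.

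**Illustration of what the open choice can be worth.** A simulation assumed 75 CHWs per arm, no clustering, no true effect and a t0–t2 correlation of 0.6. Control dropout was random, and experimental-arm dropout was more likely at low t0 scores.

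| Dropout, experimental arm | Dropout, control arm | Bias, completers only | Bias, t2 imputed from t0 |
|---|---|---|---|
| 19% | 15% | 0.10 SD | 0.00 SD |
| 33% | 30% | 0.17 SD | 0.00 SD |

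Dropout here depends only on t0 by construction, so a method that uses t0 removes the bias. The table shows that the choice of method can matter. It is not a forecast for this trial, and the second row lies well beyond the protocol's limit.

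**The case against.** The strongest reply is that the same paragraph provides for missing data. A t test can follow imputation, so the paragraph can be read consistently: keep everyone, handle the missing values, then test. A reader might infer from the named tests that everyone without a t2 score will be dropped, or that the analysis is complete-case by design. The document does not say so. That part of the reply stands, and there is no outright contradiction. What it does not do is secure the promise, because the unnamed approach need not retain everyone. For the non-parametric branch, pooling rank tests over imputed data sets is also not routine, so imputing first is not an obvious default.

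Second, withdrawing is not the same as lacking a t2 score. Dropouts are among those who may be invited to interviews on the day of t2 (Nested qualitative component), so some contact with them is planned. This also stands, although those interviews involve only two CHWs per experimental unit, and the article does not say that people who leave the course will be asked for the t2 questionnaire.

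Third, the missing-data method is commonly left to a statistical analysis plan or full protocol, neither of which is shown. The absence of a named imputation method is therefore not the point made here. The point is that the article fixes an analysis that cannot by itself meet the definition it also fixes, and that a better analysis is available at little cost.

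Fourth, these are secondary outcomes in a feasibility study that disclaims conclusions about effectiveness, and dropouts and incomplete responses will be reported. This limits the weight of the point.

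**Conclusion.** The named tests do not on their own include all participants as the definition promises. Whether the promise is kept depends on an approach to be selected according to the pattern of missingness. At the protocol's limit, up to about 22 of 150 CHWs would be absent from an observed-data t2 comparison. The bias cannot be derived from the document. Under the one-sided assumptions above it would be about 0.05 to 0.08 SD at 15% loss, and it could be nil or reversed under others.

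Three larger readings are not supported:
- A reader might apply the 30% to the 150 and expect 45 losses, leaving 105. That 30% mixes refusals with dropouts and has already been used to go from 20 units to 14.
- The 15% is a threshold for progression and should not be read as an expected loss.
- A completer analysis might be thought to overstate the SD. Nothing here shows that; losing low scorers would more typically narrow the spread.

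The point is worth acting on because the remedy is cheap and improves the estimates carried forward. It does not affect the primary feasibility outcome or the sample size.

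**What to change.** 1. Replace the t tests as the main between-group analysis of each stigma outcome with a linear mixed model on the t0 and t2 scores of all randomised CHWs with at least one score. Include arm-by-time with a common baseline mean, random effects for primary care unit and CHW, and a small-sample correction for about 14 clusters. A CHW with only a t0 score then still contributes. The unit effect and the small-sample correction are not needed for the all-participants promise as such, but they match the allocation by unit and give between-unit variance for the future trial.
2. Label any observed-data t or rank tests as descriptive completer analyses, not as intention to treat.
3. State that CHWs who leave the course will still be asked to complete the t2 questionnaire, and report t2 completion by arm.

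The cost is analysis wording, modest extra programming and some follow-up effort at t2. The model assumes that data are missing at random given baseline score and arm. If those lost differ in ways that these do not capture, some bias would remain, so the assumption should be stated with the results.

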**Ethics and dissemination:**

This study was approved by the National Commission for Ethics in Research in Brazil (n. 5.510.113). Every participant will sign a consent form. Results will be disseminated through academic journals and events related to dementia. The intervention materials will be made available online.

STRENGTHS AND LIMITATIONS OF THIS STUDYThis is the first study to develop, deliver and evaluate a controlled feasibility study of a group antistigma intervention to improve knowledge, attitudes and behaviours in relation to people living with dementia among community health workers in Brazil.This study will seek to involve all the community health workers of all the primary care units of a large urban city in São Paulo, Brazil.The study includes quantitative and qualitative components that will assess the feasibility of the intervention from different perspectives and will include a follow-up assessment, which will help us understand any potential long-term impact.As this will be a feasibility study, no conclusions can be drawn about the effectiveness of the intervention; however, we hope that the information collected will help build a robust future randomised controlled trial.

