#### Method of generating the allocation sequence

Randomisation and allocation will be conducted by blinded member of the research team at the PCU level using computer-generated random numbers. The PCUs whose managers agree to participate will be randomly allocated in two parallel groups—experimental group or control group—so that all CHWs of a given PCU who voluntarily accept to take part can be allocated in the same group forming a cluster and reducing the potential for contamination (eg, sharing knowledge learnt in the intervention between PCUs). The allocation will be made randomly at 1:1, so that there is the same number of PCUs in each group, offering as much as possible balanced participation among CHWs from PCUs located in the various geographical regions, proportional to the total number of PCUs of each region (20%: north, 20%: south, 20%: east, 20%: west, 20%: centre). The characteristics of participants (eg, age, gender, time working as CHW) will be compared between groups and controlled statistically if significant differences are observed.

Before informing the PCUs about the group to which their CHWs have been allocated, every CHWs wishing to participate will read and sign a consent form. Recruitment and enrolment will be conducted by a separate member of the team, who will be blinded to the allocation. Then, all participants will be invited to complete the baseline measures (t1). The experimental group will be informed about the dates and timings of the intervention and the control group will be told that they will be allocated to a waiting list. After the completion of the final assessments from both experimental group and control group (t2), the intervention will be offered to the control group.

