### Assessment

#### Primary and secondary outcomes

The primary outcome will be the feasibility of the intervention, including the findings of a nested qualitative component. The secondary outcomes will be the stigma-related measures: knowledge, attitudes and intended behaviour. All the outcome measures are described as follows.

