#### Baseline and poststudy assessment

Baseline (t0) and poststudy assessments (t2) will be the same for both experimental and control groups. Additional feasibility questions (closed and open questions) will be applied to the experimental group on the last day of the intervention as well as in t2, and 15–20 participants in the experimental group will be invited to participate in one-to-one semistructured interviews. Apart from the qualitative interviews, the written questions are all self-administered and will be completed on paper. Questionnaires will be distributed and collected by an assistant researcher who will be blinded to participant allocation. We hope that using anonymous self-administered questionnaires (identifiable only through participant code) will help mitigate any potential risk for social desirability bias. We will also highlight to participants that the questionnaires are not identifiable and that any answers they provide will not be linked to their names, and that they should be free to answer honestly to all the questions without any fear of being judged. The researchers applying the intervention will not have access to the participants’ responses until the end of data collection. It is expected that CHWs will take 10 min to 15 min to complete all the questions. Considering the acceptance of approximately 14 PCUs to participate in the study, it is estimated that the total period between t0 and t2 in all PCUs will be 90 days.

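### The t tests planned for the stigma scores name no single between-arm effect and leave the baseline score unused as a covariate; one baseline-adjusted estimate per domain would be more precise

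*Protocol article*

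**What the plan says.** All references are to the protocol article.

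- **Data analysis** takes differences in knowledge, attitudes and intended behaviour "before and after the intervention, between groups and between time points (t0 and t2", and says that these "will be analysed using Student’s t test or a non-parametric test, according to data distribution". It marks no comparison as the estimate of the intervention effect and names no model.
- **Baseline and poststudy assessment** shows that the covariate exists: "Baseline (t0) and poststudy assessments (t2) will be the same for both experimental and control groups".
- **Method of generating the allocation sequence** has the only provision for adjustment. Participant characteristics, with age, gender and time in the job as examples, "will be compared between groups and controlled statistically if significant differences are observed". The t0 stigma score is not among the examples. The same section allocates whole primary care units (PCUs) 1:1.
- **Primary and secondary outcomes** sets the status: "The secondary outcomes will be the stigma-related measures: knowledge, attitudes and intended behaviour".
- **Data analysis** also hypothesises that the intervention "might be able to improve knowledge, attitudes and intended behaviour in relation to dementia among CHWs", and gives as one purpose of the study "to estimate parameters needed to design the future trial".
- **The strengths and limitations box** after the abstract says that "no conclusions can be drawn about the effectiveness of the intervention".

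**The concern.** The plan lists two kinds of comparison, by arm and by time, and does not say which one estimates the intervention effect.

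The between-arm comparison is the randomised one. Made on t2 scores alone, it ignores information already collected, and with about 14 randomised units any chance baseline difference between arms passes straight into it. The t0-to-t2 comparison within an arm is not randomised. Familiarity with a repeated questionnaire, reactivity to being asked, or a general shift over the study period would all appear there as change. If the experimental arm reaches significance and the control arm does not, that pattern is easily taken for a difference between arms, which it is not.

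At stake is the quality of what the study hands on: a preliminary effect, its precision, and parameters such as the residual variance after baseline adjustment.

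**Working it through.** **Inputs from the document.** About 14 PCUs and around 150 participants (Participants and sampling), allocated 1:1, so about 75 per arm. The article gives no power or precision figure for the stigma scores, so only the planned size can be reproduced. 20 × (1 − 0.30) = 14 PCUs agrees. With 8, 10 or 12 workers per PCU, 14 PCUs give 112, 140 or 168 participants, and around 150 lies in that range.

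**Assumptions.** The document does not give the t0-t2 correlation r, the size of any common drift, or a significance level. I use r = 0.3 to 0.8, drift of 0.1 to 0.3 SD, and two-sided 5%. Scores have SD 1 and participants are treated as independent.

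**Step 1: precision of the between-arm difference, n = 75 per arm (large-sample variances).**

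- t2 score only: 2/n, so SE = √(2/75) = 0.163
- change score: 4(1 − r)/n
- adjusted for t0: 2(1 − r²)/n

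| r | SE, t2 only | SE, change | SE, adjusted | adjusted variance ÷ t2-only variance (1 − r²) |
|---|---|---|---|---|
| 0.3 | 0.163 | 0.193 | 0.156 | 0.91 |
| 0.5 | 0.163 | 0.163 | 0.141 | 0.75 |
| 0.6 | 0.163 | 0.146 | 0.131 | 0.64 |
| 0.7 | 0.163 | 0.126 | 0.117 | 0.51 |
| 0.8 | 0.163 | 0.103 | 0.098 | 0.36 |

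Adjusted against change score, the variance ratio is 2(1 − r²) ÷ 4(1 − r) = (1 + r)/2, which never exceeds 1. The change score does worse than t2 alone when r is below 0.5.

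**Step 2: within-arm test when the intervention has no effect.** The paired difference has SE √(2(1 − r)/n). At r = 0.5 and n = 75 this is √(1/75) = 0.115, so drift of 0.1, 0.2 and 0.3 SD gives noncentrality 0.87, 1.73 and 2.60. The noncentral t distribution then gives the chance of a significant result in the direction of benefit:

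| common drift | r = 0.5 | r = 0.7 |
|---|---|---|
| 0.1 SD | 14% | 20% |
| 0.2 SD | 40% | 60% |
| 0.3 SD | 73% | 91% |

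The chance that the experimental arm is significant and the control arm is not, at r = 0.5, is 0.135 × 0.865 = 12% for 0.1 SD drift and 0.401 × 0.599 = 24% for 0.2 SD.

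**Step 3: between-arm tests under the same drift.** In a simulation of 8,000 trials per setting (r = 0.6, no intervention effect, drift 0 to 0.3 SD), the t2 comparison between arms rejected in about 5% of trials throughout, and so did the baseline-adjusted comparison. Common drift therefore misleads only through the within-arm tests.

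**The case against.** The strongest reply is that these tests decide nothing. The outcomes are secondary, effectiveness conclusions are disclaimed, and the numerical decision rules under Feasibility assessment concern retention, missing outcome data and fidelity. This stands, and it limits the harm. A reader might infer that efficacy will be judged by before-and-after significance. The documents do not support that: a between-group comparison is planned as well, and no effectiveness claim is to rest on either.

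Second, the wording is loose. A t test of change scores between arms would fit it, would use t0, and would remove common drift. So it goes too far to say that the plan necessarily discards the baseline scores. What stands is that this analysis is only one possible reading, and step 1 shows that it is never more precise than adjustment.

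Third, the plan does allow statistical control. It is triggered by a significance test, does not name the t0 score, and cannot be carried out within a t test, so it does not supply the missing analysis.

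Fourth, a reader might count the possible tests and work out a chance of at least one false positive. The protocol does not list the tests, and they would share the same scores, so a figure that treats them as independent is not supported. None is offered here.

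Finally, the gain of 1 − r² ignores allocation by PCU. With clusters it also depends on the correlation at PCU level, so the ratios are indicative and not the exact gain in this design.

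**Conclusion.** The point holds as an improvement to a secondary, non-confirmatory analysis. The article itself fixes the type of test, so this is not a detail left to another document. It designates no contrast and leaves a covariate that it already collects out of the analysis.

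- **Precision.** A t2-only comparison can be replaced by one with 0.91 to 0.36 of its variance. This rests on r between 0.3 and 0.8 and on ignoring clustering.
- **Interpretation.** Under a modest common drift, the within-arm test in the experimental arm is significant in about 14% to 73% of trials with no intervention effect. This rests on r = 0.5, 75 per arm and drift of 0.1 to 0.3 SD. The between-arm comparison is not affected.
- **Reach.** The consequence is confined to the preliminary effect estimate and the design parameters for the future trial. The documents do not support a claim that progression or an efficacy conclusion depends on these tests.

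**What to change.** In Data analysis, for each of knowledge, attitudes and intended behaviour, replace the t tests with one between-arm estimate: the t2 score regressed on arm and the participant's own t0 score. The article has no model that accounts for allocation by PCU, so it should be specified here, with a small-sample correction suited to about 14 clusters.

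Report the adjusted difference with its 95% CI. Adjust for t0 in every case, regardless of any significance test at baseline, and bring the sentence on conditional control of characteristics into line with this. Report change from t0 to t2 within each arm descriptively, without tests.

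The cost is a change of analysis wording. No extra data, visits or participants are needed.

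### The study is meant to estimate parameters for a future trial, yet the only method fixed for comparing stigma scores is a data-chosen significance test, with no between-group estimate and interval named

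*Protocol article*

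**What the plan says.** All references are to the protocol article.

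- **Strengths and limitations box:** because this is a feasibility study, "no conclusions can be drawn about the effectiveness of the intervention".
- **Data analysis, first paragraph:** the aim is to evaluate trial processes and "to estimate parameters needed to design the future trial". The same sentence says: "The purpose of a feasibility study is not to make a formal analysis of the primary outcome".
- **Primary and secondary outcomes:** "The primary outcome will be the feasibility of the intervention", and "The secondary outcomes will be the stigma-related measures: knowledge, attitudes and intended behaviour".
- **Data analysis, second paragraph:** differences in the stigma scores "between groups and between time points (t0 and t2), will be analysed using Student’s t test or a non-parametric test, according to data distribution". The non-parametric test is not named.
- **Same paragraph, on summaries:** "Descriptive analysis will include central and dispersion measures", chosen to suit each variable's type and distribution. Levels of variance, reliability and correlations are also planned.

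The article names no between-group effect measure and no confidence interval.

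**The concern.** A feasibility trial that feeds a later trial should deliver a between-group difference on the score scale, the uncertainty around it, and the SD. A significance test delivers none of these by itself. Letting the observed distribution choose the test adds a second problem: whether the comparison ends up on a usable scale depends on the data. The non-parametric branch is a real possibility, since the scores come from Likert items and the plan itself intends to look for ceiling and floor effects. A rank test, the usual reading of that branch, does not estimate a difference in means.

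Two things are at stake. A result labelled significant or not significant may be read as the efficacy verdict that the article disclaims. And those designing the next trial may have a test result where they need a difference and its interval.

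**Working it through.** **1. The plan's own figure.** Participants and sampling gives 20 eligible units, 8 to 12 workers per unit, and 30% refusals and dropouts.

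- Units: 20 × 0.70 = 14, as stated.
- Workers: 14 × 8 = 112 to 14 × 12 = 168, midpoint 140. The stated figure of around 150 lies inside this range.

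The sample size is therefore a count of who is available. The article gives no alpha, power, effect size, SD or intracluster correlation (ICC), so there is no power calculation to reproduce.

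**2. Purpose against method.**

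| Needed to plan the next trial | Where the article provides it |
|---|---|
| SD of the scores | Dispersion measures and levels of variance are planned |
| Mean by arm | Likely for symmetric scores; not assured for skewed ones, because the summary follows the distribution |
| Between-group difference with its uncertainty | Not named; a test stands in its place |

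The gap is the third row, and partly the second if the data are skewed.

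**3. What an interval would show.** Inputs from the article: about 150 workers, 14 units, 1:1 allocation by unit. That gives n = 75 workers and 7 units per arm, and m = 150/14 = 10.7 workers per unit. Assumptions: ICC 0.02, 0.05 and 0.10; total SD set to 1; equal unit sizes; no further loss.

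- Design effect: DE = 1 + (m − 1) × ICC
- Standard error of the difference: SE = √(2 × DE / n)
- Half-width: t(0.975; 14 − 2 = 12 df) × SE, with t = 2.179

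| ICC (assumed) | DE | SE | 95% half-width |
|---|---|---|---|
| 0.02 | 1.194 | 0.178 | 0.39 SD |
| 0.05 | 1.486 | 0.199 | 0.43 SD |
| 0.10 | 1.971 | 0.229 | 0.50 SD |

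For illustration, at ICC 0.05 an observed difference of 0.30 SD would have an interval from 0.30 − 0.43 = −0.13 to 0.30 + 0.43 = 0.73 SD. A bare report of no significant difference would hide that range.

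**4. Why the interval must be at unit level.** An interval that treats the 150 workers as independent has half-width 1.96 × √(2/75) = 0.32 SD. Against 0.39 to 0.50 SD, that is too narrow by 1 − 0.32/0.39 = 18% to 1 − 0.32/0.50 = 36%. The interval that comes with an ordinary t test would therefore understate the uncertainty under these ICCs.

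**The case against.** The case on the other side is substantial, and most of it stands as a limit on the point.

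- **The article never says that only a p-value will be reported.** A t test is commonly reported with its mean difference and interval, and a fuller document may say so. This stands for the t branch. It does not answer the rank branch, nor the fact that the article fixes a method without naming an estimate.
- **A reader might infer that the plan contradicts its own statement about formal analysis.** It does not. That sentence concerns the primary outcome, which is feasibility; the stigma scores are secondary. Nor does the effectiveness disclaimer forbid exploratory testing; it limits interpretation. The tension is with the estimation purpose.
- **A reader might infer that the next trial will have no sizing inputs.** Dispersion and variance are planned, so SDs should exist. What is missing is the contrast with its uncertainty.
- **A reader might infer that p-values drive progression.** The provisional rules under Feasibility assessment use retention, missing outcome data and fidelity only. The final decision, though, is left to team discussion of the collated findings, and nothing excludes test results from it.
- **A reader might infer that the planned test will most likely come out non-significant.** The article gives no effect size to support that. For an assumed true difference of 0.3 SD, the ordinary t test rejects about 45–46% of the time for ICC 0.02 to 0.10; at 0.5 SD it rejects about 78–84%. The lower figure of 28% at 0.3 SD and ICC 0.05 belongs to a cluster-adjusted test that the plan does not name. A further 30% loss at t2 would probably double-count, since the stated 30% already covers refusals and dropouts together.

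**Conclusion.** The point holds in a limited form. The article fixes a comparison method that serves its stated estimation purpose poorly. It names a test chosen from the observed distribution, names no between-group estimate with an interval, and has a branch whose result would not be a mean difference on the score scale.

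The size is best expressed as precision: a half-width of about 0.39 to 0.50 SD for 75 workers and 7 units per arm. This rests on assumed ICCs of 0.02 to 0.10, equal unit sizes and complete follow-up of the 150. The argument does not depend on any power figure. This is a cheap improvement rather than a defect that threatens the study.

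**What to change.** In Data analysis, replace the sentence that names the tests with wording such as:

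*For each stigma outcome, the between-group difference in mean score at t2 will be reported with a 95% confidence interval that respects randomisation by primary care unit (for example, from unit means on about 12 degrees of freedom), together with SDs by arm and time point, whatever the distribution of the scores. Any significance test is secondary and exploratory and will not be used in the progression decision.*

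The unit-level interval should apply in every case, not only when scores are skewed. P-values need not be banned; it is enough that they do not stand in for the estimate.

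The cost is about two sentences of analysis text and no extra data. The downside is that the interval will be visibly wide and less emphasis falls on a p-value.
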